## Abstract

**Background:**

Graves’ disease is an independent risk factor for transient postoperative hypoparathyroidism. Besides the disease itself, preparation techniques are influential. Transient postoperative hypoparathyroidism has severe consequences for patients’ physical and psychological state. It can be life threatening during the acute phase and may impair patients’ health, psyche and quality of life thereafter. For the surgical therapy of Graves’ disease, total thyroidectomy is recommended according to the national S2-guideline. The evidence- based on a metaanalysis- is criticized by the Cochrane diagnostic review commentary for substantial methodological deficits. Two randomized controlled trials lead to the hypothesis that a near-total resection with bilateral remnants of ≤ 1g on each side compared to total thyroidectomy will significantly reduce the occurrence of transient postoperative hypoparathyroidism with equal therapeutic safety.

**Methods/Design:**

Patients with Graves’ disease indicated for definite surgery are eligible for the trial. Trial-specific exclusion criteria are: conservative treatment, malignancy, previous thyroid surgery and coincident hypoparathyroidism. The trial is created for therapeutic purpose through process innovation. It is designed as a prospective randomized controlled patient and observer blinded multicentered trial in a parallel design including an active comparator and an intervention group. The intervention addresses the surgical procedure: near-total thyroidectomy leaving bilateral remnants of ≤ 1g on each side in the intervention group and total thyroidectomy in the control group. The occurrence of transient postoperative hypoparathyroidism is defined as primary endpoint. Secondary endpoints are: reoperations due to bleeding, recurrent laryngeal nerve palsy, permanent hypoparathyroidism, recurrent disease, changes of endocrine orbitopathy and quality of life within a one-year follow-up period. The primary efficacy analysis follows the intention-to-treat principle. A binary logistic regression model will be applied. Complications and serious adverse events will be descriptively analyzed.

**Discussion:**

The trail is expected to balance out the shortcomings of the current evidence. It will define the surgical gold standard for the surgical therapy of Graves’ disease. Patients’ safety and quality of life are assumed to be enhanced. Therapy costs are likely to be reduced and health care optimized. The conduction of the trial is feasible through the engagement and commitment of the German association of endocrine surgeons and the National Network for Surgical Trials.

**Trial registration:**

German clinical trials register (DRKS) DRKS00004161

## Background

Graves’ disease has been identified as an independent risk factor for transient postoperative hypoparathyroidism in retrospective trials. It was confirmed by a comprehensive prospective study including 5,846 consecutive patients in 2003 [1]. In the only existing randomized controlled trial, transient hypoparathyroidism is reported with an incidence of 28% after total thyroidectomy for Graves’ disease [2]. The estimated prevalence is calculated with 2,000 patients per year according to the available data [2-4]. The underlying causes are complex. Preparation techniques, especially the extent of resection seem to be more influential than inadvertent parathyroidectomy [1,5]. Postoperative hypoparathyroidism seriously affects physical health, wellbeing and quality of life. Acute hypocalcaemia can cause cramping, bronchial spasms, cardiac and digestive dysfunction and can therefore be life threatening. Long-term effects result in cataract, conjunctivitis, pruritus, osteopenia, calcifications of the basal ganglia (Fahr’s syndrome), neurological and psychic impairments. Despite calcium and vitamin D substitution, wellbeing is predominantly impaired by anxious and phobic psychological disorders [6]. Care and treatment costs as well as the status of employee’s illness are therefore of economic relevance.

At present, total thyroidectomy is favored for definite surgery in Graves’ disease instead of subtotal resection, according to the national S2-guideline issued by the Work Group of the Scientific Medical Professional Societies (AWMF) [7]. The current evidence supporting a total thyroidectomy in Graves’ disease is based on two randomized controlled trials [2,8], one meta-analysis [9] and four retrospective trials [10-13]. All studies evaluate the outcome after total versus subtotal thyroidectomy, in relation to the incidence of recurrent disease. The meta-analysis, cited in the national S2-guideline, displayed a zero-recurrence rate and an equal risk of method-associated complications [9]. However, the corresponding Cochrane diagnostic review commentary emphasizes group inhomogeneity as a substantial methodological deficit. Four retrospective trials [10-13] demonstrated a significantly lower incidence of transient hypoparathyroidism after subtotal, compared to total resections, while the incidence of recurrent disease differed according to variable sizes of the remnants (mean 6.1 g, range 1 to 12 g) and follow-up periods. Among these four trials only one clearly defined the size of the remnant with a unilateral residual thyroid tissue of ≤ 2 g when a subtotal resection was performed [13]. With this measure, the incidence of hypoparathyroidism significantly decreased, while the incidence of recurrent disease remained unaltered within a median follow-up of 6.7 years. The recurrence rate of 0.5% in this study was attributable to inadvertently spared pyramidal lobes in all patients as the result of a systematic default. Two prospective randomized controlled trials by Witte *et al*., 2000 [2] and Barczynski *et al*., 2012 [8] again aimed at recurrence of Graves’ disease as the primary endpoint, addressing different remaining tissue volumes and resection techniques. The trial by Witte *et al*. compared two interventional arms: one arm comprised a unilateral total resection and a contralateral subtotal resection with a remaining remnant of ≤ 4 g; the second arm comprised a bilateral subtotal resection with a remaining remnant of ≤ 4 g in total to the control arm total thyroidectomy. Barczynski *et al*. considered bilateral remnants of approximately 2 g on each side. Both trials displayed a significantly lower incidence of transient hypoparathyroidism in the intervention groups. While the incidence of recurrent disease was not significant, clinically not relevant, and detectable in all affected patients six months after surgery, after a follow up of 18 to 58 months in the trial by Witte *et al*., Barczynski *et al*. reported significantly higher relapse rates within 60 months follow up. Endocrine orbitopathy did not worsen after subtotal resection in both trials. So far, the evidence from the prospective randomized controlled trials seems contradictory regarding the incidence of clinically relevant recurrent disease. Moreover, the S2-recommendation lacks appropriate evidence in view of comorbidities. According to our knowledge, the incidence of transient hypoparathyroidism has never been valued as primary endpoint. Current data suggest a relevant reduction of the incidence of transient hypoparathyroidism after a near-total resection if defined remnants of ≤ 1 g on each side are left around the posterior suspensory ligament of Berry (Ligamentum thryoihyoideum laterale). The resection will be safe compared to standard total thyroidectomy regarding recurrent disease, endocrine orbitopathy and method associated complications [2,9,13]. A prospective randomized controlled trial is necessary to define the gold standard resection for the surgical therapy of Graves’ disease in view of patients’ safety and quality of health care.

## Methods/Design

### Eligibility

Patients with Graves’ disease scheduled for definite surgery are eligible for the present study. Indications for definite surgery follow those of the national S2-guideline [7], in detail a high risk of recurrence (age below 40 years, male gender, thyroidea receptor anti-body (TRAK) serum levels > 10 U/l six months after conservative treatment, thyroid volume > 40 ml), persistent, recurrent or severe hyperthyroidism after primarily conservative therapy, thyroid growth, endocrine orbitopathy and refused radioactive iodine therapy. After a screening visit patients will be allocated into the trial according to the inclusion and exclusion criteria shown below.

### Inclusion criteria

Key inclusion criteria are: indication for definite surgery according to the national guideline, no history of previous thyroid and/or parathyroid surgery, normal vocal cord function, age greater than 18 years, expectancy of life greater than 12 months, and provision of informed consent.

### Exclusion criteria

Exclusion criteria are: eligibility for conservative treatment according to the national guideline, (suspected) malignancy, coincident hyperparathyroidism, and neurophysiological deficiencies.

### Intervention and control

The study is designed as a prospective, randomized, controlled, observer- and patient-blinded, multicentered clinical trial in a parallel design, including an intervention group and an active comparator. The intervention addresses the surgical procedure. It is defined as near-total thyroidectomy with bilateral remnants ≤ 1 g on each side for inclusion in the intervention group. After ligation of the upper pole vessels, and identification and preservation of the recurrent laryngeal nerve and parathyroid glands, the thyroid is removed from the lateral tracheal wall up to the superior suspensory ligament of Berry (ligamentum thyreohyoideum laterale). Here, the thyroid is resected leaving a piece of tissue assessed by ruler measurement accounting for 0.5 × 0.5 × 0.5 cm in size at most (≤ 1 g). After resection, the remnant *in situ* is photo documented. To ensure adequate sizes of the thyroid remnants in the intervention group, after removal of the specimen a representative piece of thyroid tissue (≤ 1 g) is excised, photo documented on a clean towel next to the ruler and weighed. This tissue fragment is later added to the specimen and both are sent for histopathology. Surgery in the control group comprises a total thyroidectomy where the whole thyroid gland must be removed [7]. The surgical sites of each side will be photo documented after resection.

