### Analysis

The primary hypothesis is whether the rate of transient hypoparathyroidism within 6 months after surgery is lower in patients after near-total compared to total thyroidectomy. A binary logistic regression model will be applied for the intervention comparison of the rates, adjusting for age, gender, hyperthyrosis and endocrine orbitopathy as additive covariates. The dropout rate can be assumed to be small, and therefore, few missing values are expected with respect to the primary endpoint. If missing values occur their reason of omission will be explored. Depending on the properties and magnitude of missing values, an appropriate estimation will be specified before the analysis of the primary endpoint. Concerning other secondary endpoints, exploratory data analysis will be performed calculating appropriate summary measures for the empirical distribution as well as calculation of descriptive two-sided 95% confidence intervals and *P*-values. Sensitivity analyses will be conducted for the per-protocol population as well as for appropriate subgroups. The safety analysis includes calculation and comparison of frequencies and rates of adverse and serious adverse events. Furthermore, statistical methods are used to assess the quality of data and the homogeneity of intervention groups.

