## Discussion

The S2-recommendation of total thyroidectomy for Graves’ disease based on the national guideline lacks appropriate evidence in view of morbidity. Total thyroidectomy compared to subtotal or near-total resection predisposes patients to a relevantly higher risk for transient postoperative hypoparathyroidism. The consequences of transient postoperative hypoparathyroidism can be severe and life threatening during the acute phase and may impair patient’s psychological state and quality of life thereafter. According to the existing evidence, near-total thyroidectomy leaving bilateral remnants of < 1g on each side is assumed to relevantly reduce the incidence of transient postoperative hypoparathyroidism with equal therapeutic safety in terms of recurrent disease, deterioration of endocrine orbitopathy and method-associated complications. The trial is likely to optimize the surgical therapy of Graves’ disease. If a lower incidence of transient postoperative hypoparathyroidism is assumed, patient’s safety and quality of life are likely to be enhanced and postoperative care and treatment will be simplified. Care and treatment costs are likely to be relevantly reduced.

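### The 0.5 cm ruler limit for the remnant is about 0.13 g, yet it is paired with ≤ 1 g, about eight times as much, so the weight check cannot enforce it

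*Protocol article*

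**What the plan says.** The section Intervention and control of the Protocol article sets the size of the remnant in three places.

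- Definition of the arm: "It is defined as near-total thyroidectomy with bilateral remnants ≤ 1 g on each side for inclusion in the intervention group".
- Operative instruction, at the ligament of Berry: "leaving a piece of tissue assessed by ruler measurement accounting for 0.5 × 0.5 × 0.5 cm in size at most (≤ 1 g"), where the weight in brackets stands as the counterpart of the dimensions.
- Verification: once the specimen is out, "a representative piece of thyroid tissue (≤ 1 g) is excised, photo documented on a clean towel next to the ruler and weighed". The stated aim of this step is adequate remnant size in the intervention group. The remnant itself is also photographed in situ.

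The weight figure recurs elsewhere. The Background bases the expected benefit on the condition "if defined remnants of ≤ 1 g on each side are left around the posterior suspensory ligament of Berry", the Abstract has "near-total thyroidectomy leaving bilateral remnants of ≤ 1g on each side in the intervention group", and the Discussion uses < 1 g per side. The 0.5 cm edge appears only once. No tissue density or conversion is given.

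**The concern.** The remnant is the intervention. The control arm leaves none, and the section Surgical methods does not restrict approach, preparation, resection approach or vessel control in either arm. Remnant size is therefore the main thing to standardise across surgeons and centres.

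A 0.5 cm cube is far smaller than 1 g of soft tissue. If the two limits differ this much, a surgeon working to the ruler and a surgeon working to the weight have very different ceilings, and each can believe that the protocol has been followed. The weighing step would not show the difference, because the only numeric limit on the weighed piece is the larger one. A reader of the results could not tell from the protocol which maximum remnant had been tested.

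**Working it through.** **Inputs.** Ruler limit 0.5 × 0.5 × 0.5 cm and weight limit 1 g, both per side (Intervention and control). Comparison remnant ≤ 2 g, from the retrospective trial described in the Background. Tissue density is not given; 0.9 to 1.2 g/cm³ is assumed as a deliberately wide range.

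**Step 1: volume under the ruler limit.** 0.5³ = 0.125 cm³ per side. This does not depend on shape: anything that fits inside those dimensions has at most this volume.

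**Step 2: mass, ratio and matching edge.** Mass = 0.125 × density. Ratio = 1 g / mass. Edge of a 1 g cube = (1/density)^(1/3).

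| Density (g/cm³) | Mass per side (g) | Both sides (g) | 1 g / mass | Edge of 1 g cube (cm) | Edge / 0.5 cm |
|---|---|---|---|---|---|
| 0.9 | 0.1125 | 0.225 | 8.9 | 1.04 | 2.07 |
| 1.0 | 0.125 | 0.25 | 8.0 | 1.00 | 2.00 |
| 1.05 | 0.131 | 0.2625 | 7.6 | 0.98 | 1.97 |
| 1.2 | 0.150 | 0.30 | 6.7 | 0.94 | 1.88 |

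**Step 3: can any density reconcile the figures?** A 0.5 cm cube weighing 1 g would need a density of 1 / 0.125 = 8 g/cm³, which no soft tissue has. The plan's pairing is not reproduced as an equivalence.

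**Step 4: a remnant between the limits.** Take 0.5 g at 1.0 g/cm³, which is 0.5 cm³.
- Definition of the arm (≤ 1 g): met.
- Operative instruction (at most 0.125 cm³): exceeded by a factor of 0.5 / 0.125 = 4.
- Weight limit on the representative piece (≤ 1 g): passed.

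**Step 5: which figure is likely to be the slip?** Two sides at the weight limit give 2 × 1 g = 2 g. This equals the remnant in the retrospective trial that "clearly defined the size of the remnant with a unilateral residual thyroid tissue of ≤ 2 g". Two sides at the ruler limit give 0.225 to 0.30 g, or 11 to 15% of 2 g. Together with the repeated use of 1 g, this suggests that the 0.5 cm edge is the figure to correct. It does not prove it.

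**Step 6: what is not affected.** The sample size does not use the remnant size. For 28% against 12%, two-sided 5% and 80% power, the calculation returns 97 per group, as stated. With 5% dropout, 97 / 0.95 = 102.1, rounded up to 103 per group, or 206 in total, as stated.

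**The case against.** The strongest reply is that nothing has been miscalculated. The text does not derive 1 g from 0.5 cm; it gives two upper bounds, and tissue within the smaller one always satisfies the larger. The ruler figure could be a cautious working target for irregular tissue that is hard to size in situ, with the bracket noting that the arm's definition is then met. On that reading the weighing step tests the defining limit of 1 g directly. The ruler limit has its own record in the two photographs, and the excised piece is meant to represent a remnant already held to 0.5 cm.

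Much of this stands. There is no strict contradiction, a surgeon who keeps to the ruler satisfies both limits, and the photographs give some separate evidence of size. But the text does not state that reading or say which limit governs. The only numeric limit on the weighed piece is 1 g, so the weight criterion cannot detect a breach of the 0.5 cm edge.

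A second reply concerns the sensitivity analyses. The section Analysis says "Sensitivity analyses will be conducted for the per-protocol population as well as for appropriate subgroups" but does not define that population, and the full protocol or analysis plan may do so. This also stands. Whether remnants between about 0.13 g and 1 g would be misclassified depends on a rule that is not shown. The point does not need that consequence.

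**Conclusion.** The concern holds. The operative limit and the weight beside it differ by a factor of 6.7 to 8.9 in mass, about 2 in edge length, over the assumed density range of 0.9 to 1.2 g/cm³. The maximum remnant under test is therefore not uniquely fixed: about 0.25 g by the ruler or 2 g by weight, for both sides together. These are ceilings, not expected amounts of tissue.

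The consequence is limited. Every compliant remnant stays within 1 g per side, and neither the intention-to-treat comparison nor the sample size changes. It should still be fixed, because the figure defines the intervention and cannot be repaired cleanly once patients have been operated on under different readings. Only the trial team can say which limit was meant.

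**What to change.** Before the first patient, the trial team should choose the intended limit and make edge and weight agree: an edge of about 1 cm with ≤ 1 g, or an edge of 0.5 cm with about 0.13 g. The same limit should apply to the remnant and to the weighed representative piece and, if remnant size is a per-protocol criterion, to that classification too. If the 0.5 cm edge is meant as a stricter working target inside a 1 g definition, the text should say so and state which of the two determines compliance.

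It would also help to record the in-situ dimensions of each side on the case report form, if the full protocol does not already require it.

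The cost is a change of wording and at most a few form fields. The ruler measurement, weighing and photographs are already planned.

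### The only weight recorded to verify remnant size is that of one substitute fragment itself specified as ≤ 1 g, and the ruler limit on the actual remnant does not correspond to 1 g

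*Protocol article*

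**What the plan says.** All of this stands in the protocol article under Intervention and control, unless another section is named.

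- **Definition.** The intervention is "near-total thyroidectomy with bilateral remnants ≤ 1 g on each side for inclusion in the intervention group".
- **Ruler.** The surgeon resects "leaving a piece of tissue assessed by ruler measurement accounting for 0.5 × 0.5 × 0.5 cm in size at most (≤ 1 g"). This step concerns the remnant itself.
- **Photograph, then weighing.** The remnant in situ "is photo documented. To ensure adequate sizes of the thyroid remnants in the intervention group", and the sentence goes on: "after removal of the specimen a representative piece of thyroid tissue (≤ 1 g) is excised, photo documented on a clean towel", beside the ruler, and weighed.
- **Fate of the weighed piece.** "This tissue fragment is later added to the specimen and both are sent for histopathology".
- **Control arm.** "The surgical sites of each side will be photo documented after resection".

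The Analysis section adds: "Sensitivity analyses will be conducted for the per-protocol population as well as for appropriate subgroups". The article does not say how the per-protocol population is defined.

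**The concern.** The intervention is defined by a weight, and only one step produces a weight. That step weighs tissue that was never left in the patient, and the tissue carries in its own specification the limit it is supposed to test. The text also speaks of one piece, while there are two remnants, and does not say how the piece is matched to either.

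What is at stake is the label on the result. The hypothesis is that remnants of at most 1 g per side reduce transient hypoparathyroidism with equal safety. Size matters on the article's own account: the Background reports significantly higher relapse rates within 60 months in a randomised trial that "considered bilateral remnants of approximately 2 g on each side". If the remnants left in this trial were larger than the definition allows, the recorded weights might not show it. The findings on hypoparathyroidism and recurrence would then be credited to an operation other than the one performed.

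**Working it through.** **1. What each step can show.** Inputs are the three size-related steps in Intervention and control.

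| Step | Tissue examined | Yields a weight? | Can it show a remnant above 1 g? |
|---|---|---|---|
| Ruler, at most 0.5 cm in each dimension | the remnant | no | yes, through its dimensions, if they are recorded |
| In situ photograph | the remnant | no | only roughly; no ruler in the frame is stated |
| Weighed piece, specified as ≤ 1 g | removed specimen | yes | not if the specification is a cap |

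Take true remnants of 0.5 g and 2 g. If the piece is capped at 1 g, its recorded weight is at most 1 g in both cases. The check gives the same answer whether or not the limit was kept. If one side is 0.5 g and the other 2 g, a single piece cannot match both.

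**2. The article's own equivalence.** It places ≤ 1 g in brackets after 0.5 × 0.5 × 0.5 cm.

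- Volume: 0.5³ = 0.125 cm³.
- Weight = volume × density. The article gives no density; I assume 1.0 to 1.1 g/cm³. Then 0.125 × 1.0 = 0.125 g and 0.125 × 1.1 = 0.1375 g, about 0.13 g.
- Ratio of 1 g to this: 1/0.125 = 8.0 and 1/0.1375 = 7.3.
- Edge of a cube weighing 1 g: (1/1.0)^(1/3) = 1.00 cm and (1/1.1)^(1/3) = 0.97 cm, about twice the stated 0.5 cm.

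A remnant within the ruler limit is therefore below 1 g by a wide margin. The converse fails: a remnant, or a weighed piece, can be 7 to 8 times the ruler limit and still satisfy 1 g. The two figures do not describe the same limit.

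**3. Sensitivity of weight to linear error.** Weight scales with the cube of linear size.

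- True dimensions 10%, 20% or 26% larger than judged: 1.10³ = 1.33, 1.20³ = 1.73, 1.26³ = 2.0 times the weight.
- Dimensions judged 10%, 20% or 26% too small: 1/0.9³ = 1.37, 1/0.8³ = 1.95, 1/0.74³ = 2.47 times.

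What this implies depends on the starting limit. From an intended 1 g, a true size 26% larger gives 2 g. From the ruler limit, the same error gives 0.125 × 2.0 = 0.25 g to 0.1375 × 2.0 = 0.275 g. Reaching 2 g from the ruler limit needs an edge of (2/1.1)^(1/3) = 1.22 cm to (2/1.0)^(1/3) = 1.26 cm, about 2.5 times 0.5 cm in every dimension.

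I attach no power figure. The article gives no frequency of oversized remnants, and an oversized remnant need not carry the control-arm risk.

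**The case against.** The strongest reply is that the weighed piece is the third of three steps. The same section requires a ruler assessment of the remnant itself and a photograph of it in place. Both are direct, if imprecise, records of what was left. This stands. A reader might infer that the trial has no means of showing that the near-total operation was delivered, or that no trial data could reveal an oversized remnant. The article does not support that.

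Second, the bracketed ≤ 1 g may not be a cap. It may state the weight expected of a piece cut to represent the remnant. Weighing would have little purpose if the result were fixed in advance, and a piece truly matched to a 2 g remnant would expose it. This reading is possible, so the wording is ambiguous. It does not rescue the step as written, because nothing says how the piece is matched, and there is still one piece for two sides.

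Third, a reader might infer that a modest ruler error brings remnants to the 2 g per side of the trial with more relapses. That follows only if 1 g is the working target. Under the stated ruler limit it would take about 2.5 times the permitted size in every dimension.

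Fourth, a reader might infer that the per-protocol analysis cannot separate delivered from undelivered operations. The article gives no per-protocol definition. Adherence rules and photograph review commonly sit in the full protocol or analysis plan, which are not shown, so their absence here is no finding.

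**Conclusion.** The point holds in a limited form. The only weight recorded belongs to a substitute fragment. Read literally, it cannot exceed the limit that defines the intervention, and it covers two remnants with one piece. It does not by itself verify remnant weight. Verification rests on the ruler assessment and the in situ photograph, and the ruler limit differs from 1 g by a factor of 7.3 to 8.0 (assumed density 1.0 to 1.1 g/cm³). Which figure defines the intervention is for the sponsor to settle; the article must be reconciled on this.

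The conclusion rests on reading the bracketed ≤ 1 g as a specification of the piece. If it is only an expected value, the weight carries some information, but the missing matching rule and the single piece remain. No bias or loss of power can be quantified from the article, and the intention-to-treat comparison remains valid for the operations as performed. What is weakened is the evidence that these operations were the one named. The change is worth making because it costs so little.

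**What to change.** 1. Reconcile the ruler limit and the weight limit in Intervention and control, so that one stated limit defines the intervention.
2. Record length, width and depth of each remnant, and include the ruler in the in situ photograph that is already taken.
3. Cut one piece per side from the removed specimen to match those recorded dimensions, with no weight cap on the piece. Record both weights whatever they are.
4. Report the distribution of the side-specific weights in the intervention arm as evidence of the operation delivered.
5. Treat any use of these weights to define the per-protocol set as supportive only. They exist in one arm and are measured after randomisation, so excluding patients on them would break the symmetry of the comparison.

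The cost is wording in the operation note and case report form, a second small piece from tissue already removed, and a minute or two in theatre. Matching error remains, since the weight is still that of a substitute. The primary intention-to-treat analysis and the sample size are unaffected.
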